## Discussion

Participation in regular physical activity shown to be related to improved health outcomes, reduced health care costs, and reduced disease risk (e.g., cardiovascular disease, Type 2 diabetes). Healthcare professionals including midwives, nurses and patient assistants are often involved in providing health-related behaviour change advice, yet their own health behaviour is relatively poor as demonstrated in occupational studies [7–9]. The *PATHS* study will examine the effectiveness of a web-based intervention evaluating different behavioural strategies to increase physical activity. The primary aim of the current trial is to test the main and additive effects of different theoretically-derived BCTs – motivational, self-regulatory and habit-based strategies – on physical activity and a range of secondary outcomes. We hypothesise that the habit condition, which includes the highest number of BCTs will be the most effective. However, we also acknowledge the potential for a larger number of BCTs may create problems for messages to be assimilated and recalled due to the relatively large amount of information provided. The greater information load may undermine, or even overturn, the effects of the BCTs on behaviour change. In addition, the current design does not allow for tests of interactions among sets of BCTs, rather the approach is focused on additive effects i.e. whether motivational interventions that include additional components (e.g., BCTs related to habit) are more effective compared to those that do not. However, this does not rule out the possibility of interactions among the different components affecting the result. Research aimed at identifying the optimum number and combination of BCTs is required to inform the design of future complex interventions.

In addition, the current study will focus on testing theoretically-distinct groups of techniques and their additive effects on health behavior change. The findings of the study will enable us to evaluate the potential mechanisms by which BCTs derived from motivation, volition and habit theories affect change in health-related behaviour. Our research will also enable us to test the mediators of the intervention effects to increase participants’ physical activity and quality of life, and to reduce work-related stress and absenteeism. We will be able to do this by comparing the effects of each intervention component (e.g., self-regulation) on outcomes mediated by specific theory-based psychological constructs (e.g., planning, self-efficacy) conceptually related to the component.

Personal characteristics of the intervention participants will be assessed to determine for whom the different intervention content is most suitable. Potential moderators of intervention effects will include level of engagement in the program and planning skills. Determining the characteristics of potential users will enable the future matching of participants with the most suitable intervention content. In addition, by providing opportunity for participants to report on the usability of the platform in healthcare professionals, we will be able to ascertain the extent to which the online intervention is feasible in this population and whether it would likely be used by the target population if it were rolled-out on a large scale.

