**Fig. 2 Fig2:**
[figure not shown]
*PATHS* study – intervention screenshots – content examples

All participants will also have access to *Frequently Asked Questions* page, a sub-section of the website about practicalities of its use (e.g., how to change their password, basic features, tips on navigating through the website). This sub-section of the website has been designed based on piloting previous similar website [66]. Participants will be able to contact an intervention facilitator if they have any additional questions about participating in the study. There will also be an *About* page available – a sub-section of the website that will (1) explain the reasons why the intervention was developed and (2) introduce the *PATHS* study research team to add credibility. A *Frequently Asked Questions* page and an *About* page, also developed from previous investigations piloting the platform, will be slightly different for each intervention condition to account for the differences between conditions.

Participants allocated to the three intervention groups will have access to additional intervention features. Each fortnight, they will be prompted via email to access the website and to answer short online surveys and receive tailored feedback based on the information provided in their responses. Depending on their group allocation (Tables 1 and 2), participants will receive feedback aimed at promoting motivation (motivation group), motivation and self-regulation (self-regulation group), or motivation, self-regulation and prompts for actions (habit group). Information pertinent to the participant’s condition will be delivered via personally-tailored messages presented as text on a webpage accompanied by appropriate pictures and graphs with tailored information (e.g., graphs showing participant’s change in physical activity or weight throughout the intervention). The intervention will include six consecutive sessions that will be presented fortnightly for three consecutive months.

**Table 1 Tab1:** Intervention content for *PATHS* study **-** overview

Session number	Motivation condition	Motivation + self-regulation condition	Motivation + self-regulation + habit condition
1	Motivation and self-efficacy	Motivation, self-efficacy and self-monitoring	Motivation, self-efficacy, self-monitoring and habit development
2	Goal setting	Goal setting and action planning	Goal setting, action planning and forming positive habits

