#### Physical activity

The primary outcome will be measured physical activity over a one-week period prior to the intervention (Time 1) and for a further week immediately post-intervention at the three-month follow-up occasion (Time 2) using accelerometers (GENEActiv Ltd.) [47, 67]. Participants will be asked to wear the unit continuously for the seven day period on the non-dominant upper arm to comply with hospital hygiene regulations. The GENEActiv device is water proof and participants will be informed that they are free to choose whether to wear it while swimming, showering, or sleeping. Data will be collected at 60 Hz epoch frequency. Step counts will be derived from the acceleration data using open-source macros and they will be used as proxy for physical activity [47]. Participants will be supplied with a band specifically designed to fasten the monitor to the upper arm.

Secondary outcomes will be assessed at baseline (Time 1) and post-intervention (Time 2), and will include subjective measures of physical activity, sitting time, sleep, depression, anxiety, stress, quality of life, theory-derived correlates of physical activity and self-reported weight. Demographics, perceived neighbourhood environment, personal need for structure, internet self-efficacy, and planning skills/ability will be assessed at baseline (Time 1) only. Secondary outcomes assessed only at the post-intervention stage (Time 2) will include measures of intervention accessibility, usefulness and satisfaction with the intervention, as well as acceptability of the advice provided. Participants’ website usage (e.g., time spent on pages with specific intervention content, number of website visits) will be assessed throughout the study using Google Analytics.

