### Sample size

Reviews of behavioural intervention studies have reported small to medium effects of web-delivered interventions aimed at increasing physical activity [84, 85]. Studies that excluded participants who are already active, which most closely represent the current protocol, reported a small-to-medium effect (*d* = 0.28) [84]. Therefore, to detect a similar effect on physical activity between intervention and control group, a total of 134 participants will be required to achieve 80% power with alpha set at *p* < .05. Based on an estimated drop out of 30% from web-based tailored interventions to increase physical activity [84], the final target sample size of 192 participants (48 per group) will be recruited at baseline. The study is powered to detect differences between the intervention group and control group (i.e., parallel 2-arm trial); not between the four study arms.

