### Study hypotheses

We hypothesise significant increases in physical activity between baseline and 3-month follow-up in the three intervention conditions but no change in physical activity levels in the control groupWe hypothesise that increases in physical activity at 3-month follow-up will be greatest in the habit intervention condition with smaller changes for the self-regulation and motivation conditions.We hypothesise that participants allocated to the habit condition will have maintained the physical activity changes over time relative to the self-regulation, motivation, and control conditions at 3-month follow-upWe hypothesise that higher engagement in the program (e.g., frequency of logins, number of sessions completed, reported relevance and usefulness of the sessions content) will lead to greater change in physical activity at 3-month follow-up in all intervention groups.We hypothesise that the effects of the habit condition on physical activity behaviour will be mediated by the self-reported habit development, effects of the self-regulation condition will be mediated by self-efficacy and planning, and the motivation condition will be mediated by the social cognitive variables of attitudes, motivation, and intention.

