### Study analysis

The intervention will be evaluated following the recent guidance on process evaluation for complex interventions [86]. Data will be analysed using generalized linear mixed modelling (GLMM) [87] with a 4 (condition: control, motivation, self-regulation, habit) × 2 (time: baseline, 3-month follow-up) mixed-model design, accounting for nesting within hospital. Models will be conducting to compare change between conditions of the primary outcome (physical activity) and secondary outcomes (e.g., theory-derived psychological constructs, DASS21, MOS-SF12, and absenteeism). Mediation analyses will be conducted using path analytic models using Preacher and Hayes’ bootstrapped approach for multiple mediation [88]. Separate path models will be conducted for each condition. Each condition will be represented by a dichotomous dummy-coded variable (0 = did not receive intervention component, 1 = received intervention component). Each condition variable will be set as a predictor of physical activity at follow up with motivation and intention (motivation condition), perceived behavioural control and planning (self-regulation condition), and self-reported habit (habit condition) as multiple mediators in each analysis, respectively. Baseline physical activity will be included as a control variable. Intention-to-treat (baseline carried forward) will be utilised for missing data from drop-out. Other missing data will be imputed using multiple imputation with chained equations [89]. Both intention-to-treat and completers analyses will be reported.

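### Engagement is measured after allocation and is self-selected, so it should not be listed as a moderator or credited with causing change; carrying baseline forward could add a spurious dose association

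*Protocol article*

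**What the plan says.** All places are in the protocol article.

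- **Discussion.** In a paragraph on which participants the content suits, the article says: "Potential moderators of intervention effects will include level of engagement in the program and planning skills".
- **Measures, Physical activity.** The two named moderators differ in timing: "planning skills/ability will be assessed at baseline (Time 1) only", whereas website usage "will be assessed throughout the study using Google Analytics".
- **Study hypotheses.** Hypothesis 4 defines engagement through logins, sessions completed, and rated relevance and usefulness of the sessions. It says that higher engagement "will lead to greater change in physical activity at 3-month follow-up in all intervention groups". Hypothesis 1 expects activity to rise in all three intervention conditions.
- **Intervention delivery.** "Participants allocated to the three intervention groups will have access to additional intervention features". These are the fortnightly sessions with tailored feedback, six in all. Control participants log in too, and under Control condition they rate Library articles.
- **Study analysis.** "Intention-to-treat (baseline carried forward) will be utilised for missing data from drop-out". The section ends: "Both intention-to-treat and completers analyses will be reported". It names no separate model for engagement.
- **Sample size.** The recruitment target of 192 (48 per group) is "Based on an estimated drop out of 30% from web-based tailored interventions".

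**The concern.** A moderator that shows for whom an intervention works must be fixed before allocation, or at least be unaffected by it. Engagement meets neither condition. It accrues during the three months, and the content that drives it differs by arm. It therefore cannot serve the purpose the Discussion gives it, which is to match future users to content.

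Hypothesis 4 has a second difficulty. Condition is randomised, but engagement within a condition is not. Participants who log in more may be those who were more motivated from the start. A causal statement about engagement does not have the support of the randomisation.

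The missing-data rule can make this worse. Carrying baseline forward gives every drop-out a change of exactly zero. If drop-outs are also the low engagers, low engagement is paired with zero change, and a positive slope follows whenever completers improve for any reason. The trial could then report a dose effect that does not exist.

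**Working it through.** **1. The plan's own figures.** 134 / (1 − 0.30) = 191.4, rounded up to 192, or 48 per arm. The three intervention arms hold 3 × 48 = 144. Expected drop-outs among them are 0.30 × 144 = 43.2, taken as 43, which leaves 101 completers. The plan gives no figure for the engagement analysis.

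**2. Assumptions not in the documents.** SD of change = 1. Completers' mean change m is unrelated to sessions and ranges from 0 to 0.5 SD. Drop-outs complete 0–3 of the six sessions, uniformly. Completers complete either 3–6 (overlapping) or 4–6 (separated), uniformly. The value 0.28 is borrowed from the Sample size section, where it is an intervention-versus-control effect and not a mean change; 0.5 has no source in the documents.

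**3. Expected slope with no dose effect.** Let p = 43/144 = 0.299, so p(1 − p) = 0.209. Drop-outs have change 0 and completers have mean m.

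- Overlapping case: mean sessions are 1.5 and 4.5, a gap of 3, with variance 1.25 in each group.
- Covariance of sessions and change = 0.209 × 3 × m = 0.628m.
- Variance of sessions = 1.25 + 0.209 × 9 = 3.13.
- Slope = 0.628m / 3.13 = 0.20m per session: 0.056 SD at m = 0.28 and 0.10 SD at m = 0.5.

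The true slope is zero, and the artefact is proportional to m.

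**4. How often it is significant.** Simulation of sessions against change, counting significantly positive results (two-sided p < 0.05, so nominal 2.5%), with 30% drop-out:

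| Analysis | m = 0 | m = 0.28 | m = 0.5 |
|---|---|---|---|
| Carried forward, n = 144, overlapping | under 1% | 25% | 74% |
| Carried forward, n = 144, separated | under 1% | 30% | 87% |
| Carried forward, one arm, n = 48 | under 1% | 7–8% | 25–30% |
| Completers only | about 2.5% | about 2.5% | about 2.5% |

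Repeated runs differ by a point or two, so I quote 24–30% and 73–87% for 144 participants, and about 8% and 25–32% for one arm. At 15% drop-out with separated session counts the n = 144 rates are about 8–9% and 44–47%.

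**5. When it disappears.** If drop-out is unrelated to engagement, total rejection (both directions) is about 5%, which is nominal. If m = 0 it is about 1%.

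**6. Self-selection among completers.** With 101 completers, a non-causal correlation between engagement and change of 0.1, 0.2 or 0.3 is significant in 17%, 54% or 87% of trials. Dropping the carried-forward values does not touch this.

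**The case against.** Four points can fairly be made for the plan.

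- **Controls do have some engagement data.** They log in and rate Library articles, and the Procedure section even speaks of all conditions when it describes fortnightly sessions. A reader might infer that engagement has no counterpart in control, so that no interaction with condition can be estimated. The documents do not support that for logins. It holds only for tailored sessions and their ratings. What stands is that Library use is not exposure to the tailored program.
- **Hypothesis 4 is already confined to the intervention groups**, and the Discussion sentence can be read the same way. This stands; a contrast with control is not necessarily planned.
- **The artefact is not certain.** A reader might infer that the carried-forward rule always produces a false dose effect. It does so only if the rule is applied to hypothesis 4, mean change is positive, and drop-outs complete fewer sessions. The article states no engagement model and does not say that drop-outs engage less. Time 2 data depend on in-person meetings, whereas sessions are online and can be completed late. Hypothesis 1 does, however, expect positive change.
- **A completers analysis is also promised.** It removes the carried-forward artefact, but the text does not make it the analysis for hypothesis 4, and self-selection remains within it.

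None of this answers the core point. A measure recorded during follow-up is listed as a moderator beside a baseline one, and a self-selected exposure is given causal wording.

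**Conclusion.** The point holds in limited form. Listing engagement as a moderator and wording hypothesis 4 causally are faults in the text as it stands, and they need no assumption about numbers.

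The carried-forward artefact is conditional on the three circumstances named above. If they hold with 30% drop-out and the assumed session counts, about 24–30% of null trials across 144 participants are significantly positive at a mean change of 0.28 SD and 73–87% at 0.5 SD. Within a single arm the rates are about 8% and 25–32%. They are illustrations, not predictions.

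The reach is one secondary hypothesis and one Discussion statement. The primary randomised comparison is not affected by this point.

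**What to change.** - In the Discussion, remove engagement from the moderators. Test moderation with variables collected at baseline, such as planning skills and personal need for structure. Describe engagement as a process measure.
- Reword hypothesis 4 so that higher engagement *will be associated with* greater change.
- In Study analysis, state that hypothesis 4 is analysed within the three intervention arms on observed Time 2 data, not carried-forward values, adjusted for condition, baseline activity and baseline intention or self-efficacy. Report the result as non-causal.

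The cost is a few sentences and one exploratory model; every covariate is already collected. The trial gives up the causal dose claim. An instrumental-variable analysis with allocation as the instrument is optional and not part of this fix. It needs the assumption that allocation acts only through the measured engagement, which is doubtful here because the intervention arms also receive text messages.

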### Implications

The study described here has important implications for public health practitioners and researchers designing behaviour change interventions. The intervention will make a unique contribution to physical activity promotion and health research by testing the effectiveness of a computer-tailored web-based intervention in promoting physical activity and stress reduction in hospital workers; an under-researched group at risk of high stress. In addition, the intervention will add to theory and knowledge on behaviour change in health contexts by testing whether the inclusions of self-regulatory and habit-forming BCTs are more effective in promoting behaviour change and health-related outcomes relative to BCTs targeting motivation alone and an information only control. This is important as it will assist in elucidating the ‘active ingredients’ of the intervention and the mechanisms by which they exert their effects. The current research will also assist in identifying the key mediators of intervention effects, providing data on the mechanisms by which each intervention condition affects changes in physical activity behaviour.

## Abbreviations

BCT: Behaviour change technique
DASS21: Depression Anxiety and Stress Scale 21
IPAQ: International Physical Activity Questionnaire
PANES: Physical Activity Neighbourhood Environmental Scale
PARQ: Physical Activity Readiness Questionnaire
PATHS: Physical Activity Tailored intervention in Hospital Staff
RCT: Randomised controlled trial
SF12: Short Form 12 (Quality of Life Measure)
SMS: Short message service
SUS: The System Usability Scale
TPB: Theory of Planned Behaviour
